**Inclusion**:

- People over 18 years old.

- Amputation of a limb.

- Minimum score of 3 on the visual analogue pain scale (VAS).

- Under pharmacological treatment for pain

- Pharmacologically stable.

- Have hospital discharge.

**Exclusion**:

- Visual alterations (hemianopsia)

- Significant neurological or cognitive impairments.

- Have previously received treatment with IMG.

**Removal**:

- Changes in medications that directly affect the main variable pain.

- Changes in the use or not of prostheses during the intervention.

Currently, the main line of treatment is pharmacological. As a result, most participants will receive medical treatment. So that this is not a condition in analyzing the effectiveness of our intervention, it will be analyzed that the participants are pharmacologically stable. By pharmacologically stable we mean that during the intervention there can be no changes in the drug that directly influences the PLP. There may also be no modifications to medications prescribed for other aspects but which may condition the PLP. An example of the latter would be antidepressants, which are adjuncts to the medications provided by PLP. If there are changes in medication that do not affect the pain, the intervention will be continued.

Prior to the intervention, the participants must have the established dose of medication, usually this dose is administered gradually until stability is achieved. Therefore, medication will be one of the variables to be collected to analyze and monitor this stability.

On the other hand, the elimination criterion according to the usefulness of the prosthesis is based on the fact that if the participant is wearing prosthesis, he / she will use it during the whole intervention, and I live in reverse, since the prosthesis could be a conditioning factor to study the effectiveness of our intervention.

1. **PARTICIPANTS:**

Participants will be recruited through the reference health professional of different hospitals that have amputee units, including the Hospital de la Santa Creu de Vic, Hospital de Sant Jaume de Manlleu, Hospital Pere Virgili, Asepeyo Sant Cugat Catalonia (Spain), which will assess its eligibility according to the established inclusion criteria. Once identified, the possible participants will be notified to the principal researcher, who will contact them by telephone to offer them the opportunity to participate and send them, via online, the information sheet with the details of the study. Those who agree to participate must sign the informed consent form and be informed that they have a waiver form so that they can withdraw from the study at any time they wish. Participants will be able to start the intervention once they have been registered or are already at home.

1. **TYPES OF SAMPLING AND RANDOMIZATION:**

A non-probabilistic sampling rate type will be used. It consists of first determining a number of subjects with certain characteristics (inclusion criteria), and then selecting the first individuals who possess these characteristics and agree to participate in the study.

As participants are recruited, an outside person will randomize them through sealed envelopes that they will assign to the control or intervention group. An external person will perform the randomization so as not to influence the assignment of the participants. During the study, the only people who will be blinded will be the evaluators so that they do not have an influence on the assessments made according to the group to which they belong. Due to the nature of the intervention, and given that the information sheet explains the characteristics of the interventions, there is no guarantee that the participants will not deduce which group they belong to. However, the therapists who will perform the intervention cannot be blinded either.

1. **PROCEDURE:**

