The data obtained as study variables will be coded at the end of the collection, processed and analyzed by the members of the research group.

The population to be used as a sample in the analysis will include all participants who meet all the inclusion criteria, do not have any exclusion criteria and have given their consent to participate in the study. If a participant leaves before completing the study, he / she will not be replaced by another participant.

In the case of participants who have not completed the study due to dropout, have not fully completed treatment, or have even changed treatment, any data that may have been collected will be analyzed for intent to treat. The minimum number of sessions to be considered for the results will be 80%.

The program to be used for statistical analysis will be the SPSS5 program. A confidence level of 95%, and / or a statistical significance p <0.05 will be considered.

If a deviation from the intended method is considered necessary during the data analysis process, the reasons for any change will be fully documented.

To describe the sample, a descriptive statistic will be performed analyzing the mean, standard deviation, minimum, maximum and percentages of the sociodemographic variables. In addition, it will be possible to look at the average of those included and excluded in order to justify the excluded people. In this way it will be possible to describe the sample and observe the homogeneity between groups.

Next, a univariate and bivariate statistical analysis will be performed. First of all, it will be assessed whether or not the study follows a normal distribution in each of the variables. This analysis will determine whether to use parametric or non-parametric tests in the analysis of results based on the "p" value.

Equality of variance will then be analyzed through the Levenne test and finally the results will be analyzed. There will be a pre- and post-intervention analysis between groups and intragroups with a three-month follow-up. We can also analyze possible correlations between variables.

Qualitative analysis:

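### The protocol does not say whether participants removed for a medication or prosthesis change are still assessed and analysed as randomised, and its removal, eligibility and intent-to-treat wording pull in different directions

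*Protocol*

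**What the plan says.** All of this is in the protocol.

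- Under *Inclusion and exclusion criteria*, a third list headed *Removal* names two events: "Changes in medications that directly affect the main variable pain" and "Changes in the use or not of prostheses during the intervention". The text below it calls the second "the elimination criterion according to the usefulness of the prosthesis".
- The same text explains the inclusion criterion of pharmacological stability: "By pharmacologically stable we mean that during the intervention there can be no changes in the drug that directly influences the PLP". It extends this to adjunct drugs: "There may also be no modifications to medications prescribed for other aspects but which may condition the PLP". It also asks that the dose be established before the intervention starts, without giving a window.
- The only consequence it spells out concerns treatment: "If there are changes in medication that do not affect the pain, the intervention will be continued".
- Under *Statistical analysis* (quantitative), the analysed sample "will include all participants who meet all the inclusion criteria", have no exclusion criterion and have consented. For people who drop out, do not finish treatment "or have even changed treatment, any data that may have been collected will be analyzed for intent to treat". Leavers are not replaced. The section also foresees comparing the people included with those excluded.
- Under *Variables*, assessments are planned at baseline, at 9 weeks and 12 weeks after the intervention. The second and third collect the dependent variables only.

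**The concern.** Both removal events happen after allocation. The stated reason for the rule is that these drugs, and the prosthesis, may influence phantom limb pain. It is plausible, though the protocol does not state it, that pain in turn prompts such changes. Participants may deduce their group and the therapists are not blinded (*Types of sampling and randomization*), so changes could also differ by arm.

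Detection may differ as well. Weekly calls are described only for the GraMI arm, while controls keep a diary of activities (*Procedure*, Step 2).

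If removed people leave the analysis, or are not visited again and so have no 9-week pain score, the remaining arms are no longer the randomised arms. The main pain comparison could then be run on different people depending on which section the analyst follows.

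**Working it through.** **Side by side.** *Removal* takes a participant out of something after a drug or prosthesis change. The intent-to-treat sentence keeps people who changed treatment. The analysis-set sentence requires all inclusion criteria, one of which is explained partly by no drug change during the intervention. No section says what removed people are taken out of, or whether their 9-week and follow-up assessments go ahead. If they are not assessed, an intent-to-treat rule that works on whatever data were collected may hold only their baseline.

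**The plan's own figure.** Inputs from *Sample size*: effect 0.81, 25 per arm, 50 in total. The printed alpha of 0.5 and beta of 0.8 are read here as two-sided 0.05 and power 0.80. That is a separate wording error; a literal alpha of 0.5 with power 0.80 needs only about 8 per arm.

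- Normal approximation: 2 × (1.960 + 0.842)² / 0.81² = 2 × 7.85 / 0.656 = 23.9, so 24 per arm.
- Noncentral t: 24.92, so 25 per arm and 50 in total. The plan's figure reproduces, with power 0.801.
- There is no stated allowance for losses. If 5%, 10%, 20% or 30% of both arms were lost for reasons unrelated to pain, power would be 0.78, 0.76, 0.70 or 0.64.

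**Illustration of pain-related removal (assumed inputs; the protocol gives no rate).** Final pain has SD 1. A trigger (pain during treatment) has correlation ρ with final pain, and a person is removed when the trigger exceeds c. Set c so that 15% of controls exceed it: c = 1.036. The mean shift among those kept is −ρ·φ(c)/Φ(c).

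*True effect 0.81, same rule in both arms:*
- Controls kept: −ρ × 0.2332/0.85 = −0.274ρ.
- Intervention arm: its threshold lies 1.036 + 0.81 = 1.846 above its own mean, so 3.2% are removed. The shift is −ρ × 0.0725/0.9676 = −0.075ρ.
- Difference among those kept: 0.81 − ρ(0.274 − 0.075) = 0.81 − 0.199ρ.
- Overall removed: (15% + 3.2%)/2 = 9.1%.

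*No true effect, 15% removed in the intervention arm only:* false benefit 0.274ρ.

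| ρ | Difference, true 0.81 (SD) | Power | False benefit under no effect (SD) | Rejection at 5% |
|---|---|---|---|---|
| 0.3 | 0.75 | 71% | 0.08 | 6% |
| 0.5 | 0.71 | 67% | 0.14 | 7% |
| 0.7 | 0.67 | 65% | 0.19 | 10% |
| 1 | 0.61 | 63% | 0.27 | 16% |

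The differences follow from the formulas. Power and rejection rates are simulated with 25 per arm, and repeat runs differ by about one percentage point. With no true effect and equal removal in both arms, the two shifts cancel: there is no bias, only lost power. If high-pain removal happened only among controls, the false difference would favour control. The prosthesis rule was not simulated.

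**The case against.** The strongest defence is that *Removal* means only stopping the intervention. The one consequence the text gives is about continuing the intervention, and the statistical section then deals with the data by intent to treat. On that reading there is no contradiction. This stands as a possible reading, so an outright contradiction is more than the text supports. It does not settle the matter: the protocol never says it, the terms removal and elimination and the planned comparison of included with excluded people point the other way, and the 9-week score could still be missing.

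Three other strong readings are tempting and not supported.

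- *A drug change in week 5 makes a randomised person retrospectively ineligible.* The literal wording allows this inference. But the protocol also requires an established dose before the intervention, eligibility is assessed before contact and consent, and nothing says it is judged again later.
- *Removal selects on the outcome.* It selects on a drug or prosthesis change, not on the pain score. The protocol gives no data on whether such changes follow worse or better pain.
- *The ρ = 1 row is the expected bias.* It assumes the trigger tracks final pain perfectly, so it is the upper end. The intervention-only case also assumes that no change is detected or acted on in controls. The protocol says medication is collected to monitor stability in participants generally. Weaker detection among controls is plausible; none at all is not stated.

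It is also fair that much analysis detail may sit in an analysis plan not seen here. The protocol itself, however, fixes the removal rule, the analysis set and the intent-to-treat rule, and these need to agree.

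**Conclusion.** The point holds as unresolved wording with a real consequence. The protocol sets post-randomisation removal rules, an analysis set tied to a criterion partly defined after randomisation, and an intent-to-treat rule, and does not say how they fit together or whether removed people are still assessed. If they are excluded or not assessed, the main pain comparison may be biased.

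The size and direction cannot be known from the document. The ranges of 0.75–0.61 SD for a true 0.81 SD, and 0.08–0.27 SD of false benefit under no effect, rest on the assumed 15% threshold, the assumed correlations, removal triggered by high pain and, for the second range, removal in the intervention arm only. Confidence is high that the sections need reconciling, and low on any particular bias figure. It should be corrected before the analysis, because it determines who is in the main comparison.

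**What to change.** Reconcile *Removal* with the quantitative analysis section:

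1. State that a medication or prosthesis change is not a reason to leave the assessments or the analysis. Invite every randomised participant to the 9-week assessment and the one 12 weeks after the intervention, and analyse each in the assigned arm.
2. Define the analysis set as all randomised participants.
3. Judge pharmacological stability for eligibility at baseline, over a window set by the investigators.
4. Record medication and prosthesis changes with dates, in the same way in both arms. A supportive analysis accounting for them is optional.

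Whether the sessions continue after a change is for the investigators; nothing here proposes a clinical rule.

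The cost is a wording change in two sections, the same recording of changes in both arms, and home visits to people who might otherwise have left. The three assessments are already in the schedule, but the protocol shows no budget for them. The small downside is that the estimated effect then includes any effect of medication or prosthesis changes made along the way.

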The researcher conducting the interview will be an external person who has not performed the intervention or randomization, so as not to influence the questions and answers. This person has theoretical sensitivity about PLP and mirror therapy and this will make it easier to delve deeper into the topics during the interviews and better understand the experience. Subsequently, two members of the research group will perform the transcripts and analysis of the results. The aim of this triangulation is to achieve the highest possible objectivity in the results. The interviews will be recorded in voice and video format in order to be able to make a transcript as optimal as possible and will help not to lose the facial and body expressions of the participant. Only the research group and the researcher who conducted the interviews will have access to the recorded material. Each participant will have previously signed the consent to the image and voice rights. Once the study is complete, the recordings will be deleted. Once the transcripts have been completed, they will be sent to each participant to corroborate the information. This process will also be performed after the analysis of the results. You can see the consent form and the interview template in the appendices.

1. **VARIABLES:**

The assessments will be carried out by two people outside the intervention and the phenomenological study. These people will be two physiotherapists with clinical experience in the field of neurorehabilitation and / or pain, trained in research methods, calibrated with each other in order to minimize bias and will be blinded by the assignment of the groups. An initial assessment, a post-intervention assessment (9 weeks) and a follow-up assessment (12 weeks post-intervention) will be performed. The assessments will be carried out in the homes of the participants, in person and will last approximately 25-30 minutes.

The variables to be studied are differentiated between sociodemographic variables, amputation characteristics, independent variables and dependent variables. The first assessment will be the one that will last longer as all the variables will be collected, but the second and third assessment will last approximately 30 minutes as only the dependent variables will be collected.

- **Socio-demographic variables**; gender, age, marital status, height, level of education, level of physical activity, pathological and traumatic history, drugs administered and dose.

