The collection of these variables will make it possible to describe the study sample and identify that the participants meet the inclusion criteria mentioned above. In this way, a sample that is as homogeneous as possible is obtained.

- **Amputation characteristics**: Cause of amputation, level of amputation, side, time since amputation, prosthetic wearer, number of hours the prosthesis is used.

- **Independent variables**: Treatment, control and intervention. All the information relevant to the conventional treatment of each of the participants will be collected.

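### Drug stability during the intervention is a safeguard to be monitored, but the written assessment schedule sets no drug record after baseline

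*Protocol*

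**What the plan says.** Under Inclusion and Exclusion Criteria, the Removal list withdraws participants whose medication changes in a way that directly affects pain. The explanatory text defines the term: "By pharmacologically stable we mean that during the intervention there can be no changes in the drug that directly influences the PLP". It extends this to drugs prescribed for other reasons that may affect phantom limb pain, such as antidepressants. The stated aim is that drug treatment should not colour the assessment of the intervention. The text then adds: "Therefore, medication will be one of the variables to be collected to analyze and monitor this stability".

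The Variables section plans three assessments: baseline, 9 weeks, and 12 weeks after the intervention. The socio-demographic list ends with "pathological and traumatic history, drugs administered and dose". On timing it says "The first assessment will be the one that will last longer as all the variables will be collected", and that "the second and third assessment will last approximately 30 minutes as only the dependent variables will be collected". The dependent variables are the short-form McGill questionnaire, EQ-5D-5L, FIM and the Beck inventory. Under independent variables it adds: "All the information relevant to the conventional treatment of each of the participants will be collected", with no time point.

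The quantitative part of Statistical Analysis keeps participants who changed treatment in the analysis by intent to treat.

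**The concern.** Stability is defined over the intervention period, so showing it needs at least one reading after baseline to compare with the first. The prose schedule takes drugs once and then restricts the later assessments to variables that do not include them. A stated collection rule therefore works against a stated safeguard.

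Two things are at stake. The removal criterion has no planned source of data, so it rests on unsolicited reports. Those reports may also reach the team unevenly: the GraMI arm has weekly telephone contact with the principal investigator, and no such contact is described for controls. Pain is the main outcome, and the protocol accepts that participants may work out their group, so changes in pain medication by arm are something a reader of the results will want to see. A later analysis plan can decide how to use such data but cannot supply data that were never collected.

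**Working it through.** There is no figure of the plan to reproduce. The check sets the promise beside each place where drug use could be recorded after baseline.

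1. **Period to be covered.** The definition of stability refers to the intervention, which Step 2 (RCT) sets at 9 weeks, followed by 12 weeks of follow-up: 9 + 12 = 21 weeks in all.
2. **Assessor visits.** There are three. Drugs and dose are socio-demographic, and the stated purpose of that group is to describe the sample and check eligibility, both baseline uses. Baseline takes all variables; the later two take only dependent variables, and medication is not one of the four listed. Stated drug readings: 1 of 3 assessments, and 0 of the 2 after baseline.
3. **Conventional-treatment information (Variables).** This may well include drugs. It has no time point, and it is classed as an independent variable, so the rule for the second and third assessments does not bring it in there.
4. **Control diary (Step 2).** It records activities with their type, frequency and duration. Drugs are not mentioned.
5. **Weekly calls (Step 2).** They check that the intervention is being done, settle doubts and encourage continuation. They are described within the GraMI protocol only, and drugs are not mentioned.
6. **App log (Step 1).** It records completion, correct answers and reaction speed, and is used only in the GraMI arm.
7. **Timetable at the end of Variables.** In the text available for this review every cell is blank, even pain at baseline, so the marks were evidently lost. It is not counted as evidence in either direction.

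A change needs two readings, and the prose provides one. For scale, each participant is 1/25 = 4% of an arm at the planned 25 per group. That is the weight of one participant, not an estimate of bias.

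Prosthesis use is in a similar position. "Changes in the use or not of prostheses during the intervention" is a removal criterion, while wear and hours appear among the amputation characteristics ("time since amputation, prosthetic wearer, number of hours the prosthesis is used") and so fall to the first assessment. The protocol makes no promise to monitor prosthesis use, so this is a side remark and not part of the finding.

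**The case against.** The strongest reply is that the restriction to dependent variables explains why the assessors' later visits are shorter. It does not forbid the research team from recording drugs elsewhere, and the diary, app log and calls are all gathered outside those visits. The commitment to collect conventional-treatment information is broad, and drug treatment is both the main line of care and an entry requirement. This part stands: a reader might infer that the trial cannot show drug stability at all, or that monitoring is ruled out. The protocol does not support that. It leaves other routes open but assigns none of them the task.

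A second reply is that the sentence promising to monitor stability directly follows one about reaching a settled dose before the intervention, so it may mean stability at entry, which a baseline record serves. That reading is possible. It fits less well with the definition two sentences earlier in the argument, which covers the intervention period. It also leaves the removal criterion, which can only operate after entry, without a data source.

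A third reply is that the timetable may show what the prose omits. That cannot be excluded. If it does mark the socio-demographic row at later visits, it conflicts with the prose and one of the two needs correcting.

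**Conclusion.** The point holds as an inconsistency between a promised safeguard and the written collection schedule. Detection of pain-relevant drug changes depends on unsolicited reports and may differ between arms. Its extent is one stated drug reading, at baseline, and none at the two later assessments. A reader might go on to infer that the treatment comparison is biased by unrecorded drug changes. The protocol gives neither a rate of change nor a difference between arms, so no size or direction of bias is claimed.

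The conclusion rests on three assumptions: the prose of the Variables section governs the visits, the unreadable timetable does not override it, and no unstated procedure already records drugs in both arms. It is worth correcting because the protocol relies on drug stability to separate the effect of GraMI from that of medication, and because the correction is small.

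**What to change.** In Variables, replace the sentence limiting the later assessments with: *At the second and third assessments the dependent variables will be collected, together with current pain-relevant drugs and dose and any change since the previous assessment, with its date. The questions will be identical in both arms.* The 9-week reading covers the period over which stability is defined; the one 12 weeks after the intervention helps interpret follow-up pain.

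In Statistical Analysis, add that changes in pain-relevant medication will be reported by arm and that intent to treat remains the main analysis. Any analysis leaving out participants who changed drugs should be labelled exploratory, because it conditions on an event after randomisation that treatment may itself influence. A question on prosthesis use at the same visits is optional.

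The cost is one short question at each of two existing visits, with no added visits or participants. Dates of change will rely on recall over 9 and 12 weeks. A reading at 9 weeks also comes too late to withdraw someone during the intervention. If removal is meant to act in real time, the protocol should add a brief drug check between visits, run the same way in both arms.
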